#### Waitlist condition timeline

Participants allocated to the waitlist condition will be sent a set of questionnaires halfway through the waitlist period to assess for symptom change and risk. If risk is detected, a member of the research team will contact the participant to assess risk and signpost if necessary. At the end of the waiting period, participants will receive another set of questionnaires to assess for symptom change and will complete a telephone assessment to re-assess for PTSD and MDD. Participants who continue with the trial will receive the intervention and assessments at the same frequency as the initial SHAPE intervention condition. A final set of follow-up questionnaires will be sent 6 months after the participant completes the intervention as well as a final telephone assessment to re-assess for long-term outcomes of PTSD and MDD.

### Sample size {19}

The sample size for the randomised controlled trial was calculated based on 90% power, at a significance level (*α*) of 0.05, to detect a difference in proportions of the number of participants continuing to have PTSD and MDD at 8 weeks post-random allocation. An anticipated recovery rate of 50% of participants in the intervention condition (i.e. 50% not recovered) and 16% of participants in the waitlist condition (i.e. 84% not recovered) corresponds to a relative risk of 0.59, requiring 39 participants per condition (78 in total). Allowing for up to 15% attrition increases the required sample size to *N* = 92 (46 participants per condition).

The effect size (50% recovery) for the intervention condition was informed by the NHS Talking Therapies target of 50% recovery for all individuals completing treatment [36]. This is a conservative estimate as findings from the pilot study of SHAPE comparing participants scores on the PCL-5 and PHQ-9 found recovery rates of 77.1% and 64.3% for MDD and PTSD respectively ([name], [name], Wilkins A, Storch C, Browne H, & [name]. Cognitive therapy coaching for PTSD and depression symptoms in healthcare workers repeatedly exposed to trauma: a pilot evaluation of SHAPE, under review). We chose a 50% recovery rate in line with the NHS Talking Therapies target and to allow for greater power for the secondary analyses. The effect size (16% recovery) for the waitlist condition was based on previous studies documenting natural recovery rates for PTSD and MDD over a 2–3-month period of between 12 and 20% for both disorders [37–40]. The 15% attrition estimate was based on dropout rates of similar trials and studies reporting rates of between 10 and 20% [37, 41–47].

Approximately *N* = 20 HSCWs will be recruited for the qualitative interview study or until a diversity of participants is reached. Purposive sampling will be used to recruit a wide range of HSCWs from the RCT who responded well and less well to the intervention. This will allow for a diversity of experiences and views to be collected and analysed. A sampling frame has been developed to ensure that there is a diversity of participants being interviewed based on gender, recruitment method, withdrawal status, recovery status, primary mental health condition, and time since trauma. The sample size for this study is guided by research informing recommendations for reaching information power [48] as well as being consistent with similar qualitative interview studies in this area [49, 50].

An additional *N* = 5 interviews will be conducted with wellbeing coaches who delivered the SHAPE intervention during the trial. *N* = 5 has been chosen based on the predicted number of coaches delivering the intervention during the trial who will be available to be interviewed.

### Recruitment {20}

Collaborating organisations that offer mental health support to health and social care workers across the UK including Canopi [51], a Welsh Government initiative to support the mental health of NHS workers, and The Ambulance Staff Charity (TASC) [52] will be invited to signpost potential participants to the trial. The study team will also use its existing networks to assist in reaching different groups of HSCWs around the UK. Self-referrals will be accepted where participants can find the trial information sheet and consent form through social media advertisements, from the research team’s website [53], trial registration website [54], blog posts, social media posts, and flyers distributed from snowball sampling by previous participants.

## Methods: assignment of interventions

### Randomisation

#### Sequence generation {21a and 21b}

After completing the telephone assessment, the second consent form, and the baseline questionnaires, participants will be randomised to one of two conditions (SHAPE or waitlist condition) on a 1:1 ratio. Randomisation will be conducted using the computer software programme Minim [55] by an independent researcher, separate to the main research team to minimise potential researcher bias. The software uses a minimisation method, and participants will be randomised based on 3 potential prognostic factors (absence/presence of PTSD using the SCID-5, depression symptom severity on the PHQ-9 (<15 or 15), and time since trauma (>/<18 months) on the PCL-5). We chose to use a median split of 15 for MDD severity using the PHQ-9 based on our pilot study where the median score on the PHQ-9 for people who were diagnosed with MDD using the SCID-5 was 15. This decision is consistent with a recent research study that dichotomised participants on the PHQ-9 with 0 for those scoring <15 or 1 for those scoring 15 or more [56]. For participants who have not experienced a traumatic event in their lives and/or do not meet criteria for PTSD, they will be asked to complete the PCL-5 in relation to the most stressful event that currently bothers them the most, indicating when this occurred. This event will be used for the time-since-trauma prognostic factor.

#### Allocation concealment mechanism {22}

The lead researcher will enter the three minimisation variables for an eligible participant into a secure excel sheet and notify the independent researcher linked to the study to randomise the participant. Once the independent researcher randomises the participant, the lead researcher will be notified of this and can then inform the participant of their condition allocation over email. Randomisation will take place in the order of when a participant completes their baseline measures.

#### Implementation {23}

The independent researcher linked to the trial will generate the allocation sequence and randomly assign participants to conditions. They will have access to a condition assignment table that other members of the research team will not be able to access, apart from the lead researcher (JL), until data collection has concluded and all participants have completed the intervention or waitlist condition. The lead researcher will be notified once a participant has been randomised and will inform the participant and their assigned coach of this outcome.

## Blinding

### Who will be blinded after assignment to interventions {24a}

Participants and coaches will not be blind to treatment allocation due to the nature of the intervention. Assessors conducting the SCID-5 assessment for treatment outcome will be blind at all post-randomisation assessment timepoints. Members of the trial steering committee will also be blind for the duration of the trial until all data analyses have been completed.

### How blinding will be achieved {24b}

Assessors conducting the post-treatment allocation assessments will be blind for the duration of the study until data lock. The research team will request participants to refrain from disclosing group allocation during post-randomisation assessments. Assessors will be instructed to refrain from asking about group allocation during assessments.

### Procedure for unblinding if needed {24c}

Assessors will be unblinded if a risk and safeguarding issue arises during an assessment and the study team deem that it is in the best interests for the assessor to be aware of what condition the participant was assigned to after the assessment has been completed.

## Methods: data collection, management, and analysis

### Plans for assessment and collection of trial data {25a}

Outcome data will be collected from all participants, including participants who withdraw from the intervention wherever possible. Furthermore, participants will be thanked with an honorarium of £20 once they complete their second SCID-5 assessment to improve data collection and completeness. In addition, for participants who withdraw or who are difficult to contact, multiple efforts will be made by the research team to reach these participants and invite them to complete measures at all data collection timepoints. Attempts will be made through different modalities (i.e. email, telephone, SMS) in case participants change contact information or are more accessible through one modality. The research team will continue to contact hard-to-reach participants throughout the trial until they complete outcome data or they withdraw consent from being sent outcome measure invitations. Shortened versions of questionnaires will also be made available to participants to complete, which will contain the most important measures (i.e. PCL-5 and PHQ-9) to reduce the potential burden on participants who struggle to complete follow-up measures. An additional monetary incentive (£10 e-voucher) for filling out a shortened questionnaire (PCL-5 and PHQ-9) will be issued for particularly hard-to-reach participants who do not respond to any contact method and who have not completed either the self-report measures or SCID-5 assessment at any post-randomisation timepoint. Most of the outcome data will be collected using Qualtrics [57], a widely used data collection online software programme. Participant outcome data on Qualtrics will be pseudonymised by participant ID. Access to the outcome data will be restricted to the main study team (JL, JW, CC, AE, and AM) using a secure login (two-factor authentication). To minimise data entry errors and ensure completeness, data validation procedures including force response settings and single-choice restrictions will be implemented within the Qualtrics survey platform where applicable. The only data that will not be collected over Qualtrics is the SCID-5 assessment measures collected at baseline, 8 weeks post-random allocation, and 6 months post-intervention completion as well as the semi-structured interviews. This data will be in the format of interview recordings, online SCID-5 assessment sheets, and online topic guides that will be safely stored in restricted access folders on Nexus 365 OneDrive for Business, only accessible by the main study team. Data completeness and anomalies will be checked on a weekly basis by the trial lead (JL), and any issues will be flagged and brought to weekly supervision with the PI (JW) to be resolved on a case-by-case basis.

### Measures

#### Primary outcome measure

Structured Clinical Interview for DSM-5 (PTSD and MDD modules) [22]. The SCID-5 is a semi-structured diagnostic interview for DSM-5 disorders and demonstrates good to excellent reliability, specificity, and validity [22]. The trial will use the SCID-5 PTSD and MDD modules. The SCID-5 PTSD module consists of 32 questions, whilst the SCID-5 current MDD module consists of 14 questions. The SCID-5 for PTSD and MDD will be administered by a trained assessor at 8 weeks post-random allocation.

#### Secondary outcome measures

Structured Clinical Interview for DSM-5 (PTSD and MDD modules) [22]. All participants, including those initially assigned to the 8-week waitlist condition, will be invited to be re-assessed for PTSD and MDD with the SCID-5 at 6 months after completing the SHAPE intervention.

Posttraumatic Stress Disorder Checklist for DSM-5 (PCL-5) [20]. The PCL-5 is a 20-item self-report questionnaire that provides a continuous measure of the severity of PTSD symptoms. Items align with the DSM-5 criteria for PTSD. Items are rated on a 5-point Likert scale (0 = not at all, 4 = extremely) and summed to provide a total score of PTSD symptom severity. Scores range from 0 to 80, with higher scores reflecting more severe PTSD symptoms. The PCL-5 is a psychometrically robust measure [20, 23]. Participants in the intervention condition will complete the PCL-5 at baseline, during the intervention (weeks 1–7), at 8 weeks post-random allocation, and at 6 months post-intervention completion for secondary analyses. Participants in the waitlist condition will complete the PCL-5 at baseline, 4 weeks, and 8 weeks post-random allocation. Waitlist participants who subsequently receive the SHAPE intervention will complete the PCL-5 at the same timepoints during and after the intervention as the intervention group.

Patient Health Questionnaire (PHQ-9) [21]. The PHQ-9 is a 9-item self-report questionnaire that provides a continuous measure of MDD symptom severity. Items are rated on a 4-point Likert scale (0 = not at all, 3 = nearly every day), and responses are summed together to reflect an overall score of MDD symptom severity. Scores range from 0 to 27, with higher scores reflecting more severe depression symptoms. The PHQ-9 demonstrates good reliability and validity [21]. Participants will be assessed for MDD symptom severity with the PHQ-9 at the same time points as for the PCL-5 for each condition respectively.

Generalised Anxiety Disorder Scale (GAD-7) [28]. The GAD-7 is a seven-item self-report questionnaire that provides a continuous measure of anxiety symptom severity. Items are rated on a 4-point Likert scale (0 = not at all, 3 = nearly every day), and responses are summed for an overall score. Scores range from 0 to 21, with higher scores reflecting more severe symptoms. The GAD-7 is psychometrically sound [24]. Participants will be assessed for GAD using the GAD-7 at baseline, 4 weeks post-random allocation, 8 weeks post-random allocation, and at 6 months post-intervention completion for secondary analyses.

Insomnia Sleep Index (ISI) [25]. The ISI is a seven-question self-report measure that provides a continuous measure of sleep quality. Items are rated on a 5-point Likert scale (0 = none, 4 = very severe), and responses are summed together to reflect an overall score of sleep quality. Scores range from 0 to 28, with higher scores reflecting poorer sleep. The ISI demonstrates excellent reliability and validity [25]. Participants will be assessed for insomnia symptoms at baseline and at 8 weeks post-random allocation for secondary analyses.

International Trauma Questionnaire (ITQ) [27]. The ITQ is an 18-item self-report questionnaire that provides a categorical and dimensional scoring system to assess PTSD and C-PTSD diagnosis and symptom severity respectively. Response items are on a 5-point Likert scale (0 = not at all, 4 = extremely). The measure has two major subscales consisting of three symptom clusters, the Posttraumatic Stress Disorder Subscale (items 1–6) and the Disturbances in Self-Organisation Subscale (items 10–15). Dimensional scores of 0–24 can be calculated for the two major subscales by summing the items to assess severity. The ITQ has been validated by Hyland et al. [26]. Cloitre et al. [27] established the optimal symptom indicators of C-PTSD and PTSD by item response theory analysis. Participants will be assessed for C-PTSD symptom severity with the ITQ at baseline, 8 weeks post-random allocation, and 6 months post-intervention completion for secondary analyses.

#### Process measures

Responses to Intrusions Questionnaire Short Version (RIQ-s) [29]. The RIQ-s is a 12-item self-report questionnaire, which assesses the frequency of maladaptive responses to unwanted memories. A total score can be calculated as well as scores for each of the three subscales: thought suppression (items 1–3), rumination (items 4–9), and numbing (items 10–12) [28, 29]. Items are rated on a 4-point scale (0 = never, 3 = always). The RIQ-s demonstrates good reliability and predictive validity [30]. Participants will complete the RIQ-s at baseline, 4 weeks post-random allocation, 8 weeks post-random allocation, and at 6 months post-intervention completion for secondary analyses.

Posttraumatic Cognitions Inventory Short Version (PTCI-s) [31]. The PTCI-s is a 20-item self-report questionnaire that assesses negative trauma-related appraisals representing cognitive themes. The cognitive themes include vulnerable self, self-criticism, overgeneralised danger, preoccupation with unfairness, perceived permanent change, alienation, hopelessness, shame, and a negative view of one’s body. Items are rated on a 7-point scale (1 = totally disagree, 7 = totally agree). A total score is the sum of all the items, with a lower score indicating better clinical outcomes [31]. The PTCI-s demonstrates good reliability and predictive validity [31]. Participants will complete the PTCI-s at baseline, 4 weeks post-random allocation, 8 weeks post-random allocation, and at 6 months post-intervention completion for secondary analyses.

#### Wellbeing and resilience measures

Warwick-Edinburgh Mental Wellbeing Scale (WEMWBS) [32]. The WEMWBS is a 14-item self-report questionnaire of wellbeing. Items are rated on a 5-point scale (1 = none of the time, 5 = all of the time). A total score is the sum of all the items, with a higher score indicating greater mental wellbeing [32]. The highest score a participant can obtain on this scale is 70, whilst the lowest is 14. The WEMWBS has good psychometric properties [32, 33]. Participants complete this measure at baseline, 8 weeks post-random allocation, and at 6 months post-intervention completion.

Connor-Davidson Resilience Scale 25 (CD-RISC-25) [34]. The CD-RISC-25 is a 25-item self-report questionnaire measuring psychological resilience. Items are rated on a 5-point scale (0 = not true at all, 4 = true nearly all the time). Scores range from 0 to 100, with higher scores reflecting greater resilience [34]. The CD-RISC-25 demonstrates good reliability and predictive validity [34]. The CD-RISC-25 will be given at baseline, 8 weeks post-random allocation, and at 6 months post-intervention completion.

Social support scales (adapted from Sarason et al. [35]). Two social support scales will measure perceived support from (i) family and friends and (ii) colleagues and superiors at work. The scale for friends and family is a 7-item self-report questionnaire with items rated on a 7-point scale (1 = never, 7 = always). The scale for colleagues and superiors is a 6-item self-report questionnaire with items rated on a 7-point scale (1 = never, 7 = always). A higher score on both scales indicates more positive perceptions of social support. Perceived social support will be assessed at baseline, 8 weeks post-random allocation, and at 6 months post-intervention completion.

#### Life and job satisfaction questions

Two questions ask participants to rate how much on a scale of 0–100 (0 = not at all; 100 = extremely) they are satisfied with their life and job at baseline, mid-intervention (week 4), 8 weeks post-random allocation, and 6 months intervention follow-up.

#### Previous trauma measures

Adverse Childhood Experiences Revised Questionnaire (ACE-Q) [58]. The ACE-Q is a 10-item self-report questionnaire that is used to quantify the number of adverse experiences a person has experienced before their 18th birthday. Items are dichotomous, rated as being yes or no. The total score is the number of yes responses. A higher score indicates that a person has experienced a greater number of childhood traumatic events. The ACE-Q has good psychometric properties [58]. The ACE-Q will be administered at baseline.

Life Events Checklist for DSM-5 (LEC-5) [59]. The LEC-5 is a 17-item self-report measure used to screen for the types of traumatic events that may have occurred in a person’s life. The response options are as follows: happened to me; witnessed it; learned about it; part of my job; not sure; doesn’t apply. Respondents can select multiple choices for each question. The LEC-5 is scored as the number of different types of trauma a person has experienced. The LEC-5 demonstrates adequate psychometric properties [60]. Participants will complete the LEC-5 at baseline.

New trauma experienced questions. Two questions will assess whether participants have experienced new stressful or traumatic events, including the nature of any such events at 4 weeks post-random allocation, 8 weeks post-random allocation, and at 6 months post-intervention completion. The purpose of these questions is to account for new trauma and its potential influence on outcome.

#### Questionnaire instruction alterations for timeframe

For the weekly administration of measures during the intervention period (weeks 1–7), we modified the PCL-5 to refer to symptoms experienced *in the past week* rather than *in the past month*. We made a similar modification to the PHQ-9 and GAD-7 for weeks 1–7 and weeks 4 and 8 respectively to refer to the experience of symptoms *over the last week* rather than *over the last two weeks*. For all other secondary measures (ISI, ITQ, RIQ-s, PTCI-s, WEMWBS, CD-RISC-25, and social support scales), we have changed the timepoint to be *in the past week* compared to the usual timepoints for these measures for weeks 4 and 8. The baseline and 6 months post-intervention follow-up assessment timepoints will use the standard timepoints for all measures.

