##### Long-term follow-up outcomes

We predict that the effects of the SHAPE intervention will be maintained at the 6-month follow-up for the primary and secondary outcome measures.

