#### Follow-up analyses

To measure the long-term effects of the SHAPE intervention, secondary analyses will be conducted for all participants who received the intervention (i.e. including post-waitlist participants going on to receive SHAPE). Secondary outcome measures for these analyses will include dichotomous SCID-5 diagnosed PTSD and MDD at 6 months post-intervention completion, and continuous symptom, resilience, and wellbeing measures collected at 6 months post-intervention completion.

To test if there is a significant difference between receiving SHAPE immediately or after waitlist, between-group analyses of the dichotomous and continuous secondary outcome measures at 6 months post-intervention completion will first be conducted. If there are no significant group differences, within-group analyses will be conducted including everyone who received the intervention. Alternatively, if there are significant group differences, separate within-group analyses will be conducted for each condition. Since participants randomised to the two conditions receive the SHAPE intervention at different starting points (i.e. immediately versus post-wait), time will therefore be coded in relation to the start of the intervention rather than time since randomisation for these analyses. Timepoints will therefore include pre-intervention (baseline or post-wait scores), post-intervention (after 8 weeks of intervention), and 6 months post-intervention completion.

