For the dichotomous secondary outcome measure, SCID-5 diagnosed PTSD and MDD at 6 months post-intervention completion, a mixed effects logistic regression model will be used. For the between-group analysis, the model will include fixed factors of time (post-intervention, 6-month post-intervention completion), condition (SHAPE, waitlist), and time × condition. Participant will be treated as a random effect. If there is not a significant difference between groups (receiving SHAPE immediately or after waitlist), a within-group analysis will be conducted that will include fixed factors of time (post-intervention, 6-month post-intervention completion), and participant will be treated as a random effect. If there is a significant difference between groups, separate within-group analyses will be conducted for each condition. The stratification variables absence/presence of PTSD based on the SCID-5, depression symptom severity (<15 or 15) based on the PHQ-9, and time since trauma (>/<18 months) based on the PCL-5 will be included as fixed covariates in all models, along with the pre-intervention diagnosis of PTSD and MDD.

For the continuous secondary outcome measures collected at 6 months post-intervention completion, mixed effects regression models will be used. For the between-group analyses (receiving SHAPE immediately or after waitlist), models will include fixed factors of time (post-intervention, 6-month post-intervention completion), condition (SHAPE, waitlist), and time × condition. Participant will be treated as a random effect. If there is not a significant difference between groups, within-group analyses will be conducted that will include fixed factors of time (post-intervention, 6-month post-intervention completion), and participant will be treated as a random effect. If there are significant differences between groups, separate within-group analyses will be conducted for each condition. The stratification variables absence/presence of PTSD based on the SCID-5, depression symptom severity (<15 or 15) based on the PHQ-9, and time since trauma (>/<18 months) based on the PCL-5 will be included as fixed covariates in all models, along with the pre-intervention score of the measure being analysed.

A detailed statistical analysis plan is available to view as a supplementary file.

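### On seven scales or scale sets the recall window changes between week 8 and 6 months, so the planned post-intervention to 6-month time effect cannot be attributed to symptom change alone

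*Protocol article*

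**What the plan says.** All quotes are from the protocol article.

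**Recall windows** (Questionnaire instruction alterations for timeframe)
- General rule outside the treatment or waiting period: "The baseline and 6 months post-intervention follow-up assessment timepoints will use the standard timepoints for all measures".
- PCL-5: "For the weekly administration of measures during the intervention period (weeks 1–7), we modified the PCL-5" to ask about the past week. Week 8 is not listed.
- PHQ-9 and GAD-7: "We made a similar modification to the PHQ-9 and GAD-7 for weeks 1–7 and weeks 4 and 8 respectively". Read in order, the PHQ-9 is altered in weeks 1–7 and the GAD-7 at weeks 4 and 8.
- ISI, ITQ, RIQ-s, PTCI-s, WEMWBS, CD-RISC-25 and social support: past week, "compared to the usual timepoints for these measures for weeks 4 and 8".

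**Follow-up models** (Follow-up analyses)
- Time is counted from the start of the intervention: "Timepoints will therefore include pre-intervention (baseline or post-wait scores), post-intervention (after 8 weeks of intervention), and 6 months post-intervention completion".
- For the between-group step on continuous measures, "models will include fixed factors of time (post-intervention, 6-month post-intervention completion), condition (SHAPE, waitlist), and time × condition". The within-group step keeps the same two time levels. All models adjust for the pre-intervention score of the measure.
- If the between-group step shows no significant difference, the arms are pooled. Otherwise each is analysed separately.

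**Hypothesis served** (Long-term follow-up outcomes): the prediction that "the effects of the SHAPE intervention will be maintained at the 6-month follow-up for the primary and secondary outcome measures".

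**The concern.** A time effect from post-intervention to 6 months is meant to show whether gains hold. On the altered scales the first of the two scores answers a past-week question and the second answers the standard one. Every participant changes window at the same step, so no covariate or random effect can separate the effect of the wording from a change in symptoms. A shift due to wording could be published as relapse or further gain, or could hide a real relapse.

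The covariate raises a second issue. The pre-intervention score is the randomisation baseline (standard window) in the immediate arm and the post-wait week-8 score (past week) in the waitlist arm. The comparison that decides pooling therefore adjusts the two arms on differently worded versions of the same scale.

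**Working it through.** **Step 1. Windows by measure, on the literal text**

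| Measure | Baseline | Week 8 | 6 months | Post vs 6 months matched? |
|---|---|---|---|---|
| PCL-5, PHQ-9 | standard | standard (only weeks 1–7 altered) | standard | yes |
| Life and job satisfaction | not among the altered measures | not altered | not altered | yes |
| SCID-5 | interview, not altered | not altered | not altered | yes |
| GAD-7, ITQ, RIQ-s, PTCI-s, WEMWBS, CD-RISC-25, social support | standard | past week | standard | **no** |
| ISI | standard | past week | not assessed | no such contrast |

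Seven scales or scale sets are affected. This assumes that waitlist participants who go on to SHAPE get the same past-week wording at week 8 of their own intervention.

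**Step 2. The protocol's sample size.** There is no stated figure for a window effect. The 78 used below is the evaluable number in the Sample size section, and it reproduces with a pooled-variance two-proportion formula (50% vs 16%, two-sided 5%, 90% power):

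n = [1.960 × √(2 × 0.33 × 0.67) + 1.282 × √(0.50 × 0.50 + 0.16 × 0.84)]² / 0.34² = (1.303 + 0.795)² / 0.1156 ≈ 38.1, so 39 per arm and 78 in total. Then 78 / 0.85 = 91.8, so 92.

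**Step 3. False time effect (illustration).** Assume no true change, a pure window shift s in SD units, a within-person correlation r = 0.6 and n pairs:

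SE = √(2(1 − r)/n); P(reject) = Φ(−1.96 − s/SE) + 1 − Φ(1.96 − s/SE)

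| n pairs | SE (SD) | s = 0.05 | s = 0.1 | s = 0.2 | s = 0.3 |
|---|---|---|---|---|---|
| 78 | 0.101 | 8% | 17% | 51% | 84% |
| 60 | 0.115 | 7% | 14% | 41% | 74% |
| 50 | 0.126 | 7% | 12% | 35% | 66% |

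With 78 pairs, r = 0.5 gives 14%, 42% and 76% at 0.1, 0.2 and 0.3 SD, and r = 0.7 gives 21%, 63% and 93%.

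**Step 4. Covariate mismatch (illustration).** If the pre-intervention score differs by s between arms through wording alone and the covariate slope is b, the adjusted condition main effect moves by b × s:
- smallest: 0.4 × 0.1 = 0.04 SD
- largest: 0.6 × 0.3 = 0.18 SD

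With 39 per arm, one time point and b equal to the correlation, SE = √((1 − b²) × 2/39), which is 0.21 SD at b = 0.4 and 0.18 SD at b = 0.6. Rejection then rises from 5% to about 5% at the smallest shift, 8% mid-range (b = 0.5, s = 0.2) and 17% at the largest. The time × condition term is unaffected, because both arms have the same windows for the outcome at both times.

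**The case against.** The strongest reply is that the affected analyses carry little weight. The protocol calls all secondary analyses exploratory, and its Discussion already accepts that 6-month changes cannot be shown to be specific to the intervention. The diagnostic, PTSD and depression parts of the maintenance hypothesis can be tested as planned. All of this stands. It limits the importance of the point but does not remove the confounding, since the limitation in the Discussion concerns the missing control group, not the questionnaire wording.

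The size is assumed. Apart from the GAD-7 (two weeks), the protocol does not say what the usual windows of the altered scales are, so even the extent of the wording change cannot be read from it. A 0.05 SD shift would barely matter. The 78 pairs are also optimistic: they come from the 8-week calculation, waitlist participants may decline SHAPE, and follow-up runs six months longer. Hence the range of 50 to 78.

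The SAP is not at hand and may contain a caveat or sensitivity analysis. That would change how the result is reported, but not the mismatch, because the windows and the model are both fixed in the protocol.

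Three stronger readings are tempting and not supported:
- *The maintenance hypothesis cannot be answered.* Even on the altered scales the contrast is confounded by an unknown amount, which is a weaker statement. On the matched measures it can be tested.
- *The pooling decision is invalid.* Only the condition main effect is touched, and modestly (Step 4). A person-level covariate does not bias the within-person time contrast.
- *The 8-week trial result is biased.* Both arms answer the same wording at week 8, so a baseline covariate on another window costs precision only.

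**Conclusion.** The point holds for the GAD-7, ITQ, RIQ-s, PTCI-s, WEMWBS, CD-RISC-25 and social support scales. On these, a post-intervention to 6-month time effect is fully confounded with the change of recall instruction and should not be read as symptom change alone. Under an assumed shift of 0.1 to 0.3 SD, the false-positive rate would lie between roughly 12–17% and 66–84%. The true shift, including its direction, is unknown and could be smaller. The covariate mismatch is secondary, worth about 0.04 to 0.18 SD on the condition main effect under an assumed slope of 0.4 to 0.6.

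The primary SCID-5 outcome, the week-8 between-arm comparison, and the follow-up of SCID-5, PCL-5, PHQ-9 and life and job satisfaction are unaffected on the literal text. This should be corrected in the analysis plan, but it does not threaten the main trial result.

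**What to change.** Recruitment is complete and data collection was due to end by December 2025, so the remedy is in the analysis and its reporting:

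1. Rest the formal maintenance test on the window-matched measures: SCID-5, PCL-5, PHQ-9, and life and job satisfaction.
2. For the seven altered scales or scale sets, report post-intervention versus 6 months descriptively, and state the window change beside the result.
3. Baseline versus 6 months may be added for these scales as a window-matched estimate. Label it total change, not maintenance, and note that in the waitlist arm it includes the 8-week wait.
4. In the immediate-versus-delayed comparison on these scales, adjust both arms on the randomisation baseline, which has one window, in place of the post-wait score.

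This needs changes of wording only and no new data. The cost is that maintenance is not formally tested on the altered scales. In the delayed arm the randomisation baseline is also eight weeks older than the start of treatment, so it may be a weaker covariate than the post-wait score.
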